#### Aim

Experiment 1 will test several predictions of GNW and IIT (detailed below): the most critical for GNW relates to its predictions concerning information about a clearly visible stimulus, the decodability of which should not depend on whether the percept is task-relevant or not; and IIT’s critical prediction that the physical substrate of consciousness should remain active throughout the presentation of a clearly visible stimulus, whether task-relevant or not.

#### Design, stimuli, and procedure

We will measure brain activity elicited by visual stimuli that are clearly consciously perceived while manipulating (1) the task, such that some stimuli are task-relevant while others are task-irrelevant [following 49], (2), stimulus duration, such that stimuli are perceived for different durations [50], (3) stimulus category, such that the content of perception varies, and (4) stimulus orientation, such that the specific features of the perceived content within a given category can be tested under fully task-irrelevant conditions.

We will use four categories of stimuli that naturally fall into two distinct classes—pictures (20 faces, half male, half female, and 20 objects) and symbols (20 letters and 20 false-fonts). Stimulus orientation will be manipulated, *i*.*e*., half will have a side view (rotated +/- 30°) and half a front view. All stimuli will be supra-threshold, presented at fixation and subtend the same size in visual angle (6°x6°).

In each 2s trial, one stimulus from one of the four categories will be presented, in greyscale, for a duration of 500, 1000 or 1500ms, followed by a blank. The experiment will be divided into mini-blocks, so that for each mini-block, half the trials will contain task-relevant stimuli and the other half task-irrelevant stimuli. To define task-relevance, subjects will be instructed to detect the occurrences of two targets regardless of their orientations (targets in both orientations will be presented at the beginning of the trial) belonging to two different categories (counterbalanced between mini-blocks) (Fig 2). Accordingly, each mini-block will contain three different trial types: i) *Task-Relevant Targets*: the two stimuli being detected in that block (e.g., a specific face and object; upper row in Fig 2; or a specific letter and a false-font; lower row in Fig 2); ii) *Task-Relevant Non-Targets*: stimuli from the task-relevant categories but not the specific targets (e.g., other faces and objects; highlighted in blue in upper row in Fig 2); and iii) *Task-Irrelevant Stimuli*: stimuli from the other categories (e.g., letters and false-fonts; highlighted in green in upper row in Fig 2). Thus, the very same stimuli will be task-relevant non-targets in some blocks and task-irrelevant in other blocks. Subjects will be asked to maintain central fixation throughout each trial. Gaze will be monitored online through an eye tracker.

**Fig 2 pone.0268577.g002:**
[figure not shown]
Experiment 1 design—In separate blocks (top & bottom rows), subjects will be asked to detect infrequent targets drawn from two categories: a specific face and a specific object (upper row), or a specific letter and a specific false-font (lower row). The stimuli will be shared across blocks, but the selection of the targets will determine to which of three trial types each stimulus belongs: *task-relevant targets*, *task-relevant non-targets*, *task-irrelevant non-targets* highlighted by red, blue and green frames respectively. Colored frames are shown for illustration purposes only. The duration (500, 1000, 1500 ms) and orientation (side view/front view) of stimuli will be manipulated to allow for specific analyses. Blank intervals between stimuli and intertrial intervals (truncated exponential distribution) are not depicted here.

Thus, in formal terms, Experiment 1 is a nested factorial design with four factors: stimulus category (face, object, letter, false-font), task relevance (task-relevant targets, task-relevant non-targets, task-irrelevant stimuli), stimulus duration (500, 1000, 1500 ms), and stimulus orientation (front view, side view). We are particularly interested in the interactions between stimulus category and task-relevance, as well as between stimulus duration and task-relevance. Trial numbers, stimulus randomization and timing parameters are optimized for the different methodologies i.e., fMRI, M-EEG and iEEG. Technique specific details are described in the preregistration in OSF.

#### Participants, sample size, exclusion criteria and stopping rule

For the fMRI and M-EEG studies, all participants will be older than 18 years old, have reportedly normal or corrected-to-normal visual acuity and no known history of psychiatric or neurological disorders. For the iEEG studies, subjects will be 10–65 years old, be able to provide informed consent, have IQ > 70, be fluent in English or Spanish, self-reported normal hearing, normal or corrected-to-normal vision, and show cognitive and language abilities within or above the normal range in formal neuropsychological testing performed before surgery and must not have had an electrographic seizure within 3-hours prior to testing. When available, information concerning language dominance as assessed by the intracarotid sodium amobarbital (Wada) will be reported.

Informed consent will be obtained prior to the study. In the case of minors, assent will be obtained from the minor and informed consent will be obtained from a parent or a legal guardian. IRB approval has been obtained from each local site in which the experiments are being conducted. Patients will be informed that participation in the study will not affect their clinical care and that they could withdraw their participation from the study at any point without affecting their clinical care. All subjects will be informed that data will be made publicly available for a minimum of 5 years after the publication of the main results. Only subjects agreeing to the data sharing procedure will be recruited.

Targeted sample sizes were determined for each methodology as being 2.5 times larger than common sample sizes in the literature for that methodology (50 subjects for fMRI and for M-EEG given that 20 subjects is the common sample size; 25 subjects for iEEG given that 10 subjects is the common sample size). Samples sizes refer to total data that will be collected in each individual laboratory, i.e., total sample sizes when the data is combined across labs will be one hundred for fMRI, one hundred for M-EEG, and fifty for iEEG. We estimate a 20% attrition related to data quality. Even after considering attrition, since we will use a within-subject design, this sample size will give us >90% power to detect differences of medium effect size (Cohen’s d = >0.5).

The data will be analyzed by the data monitoring team (who are not part of the data acquisition labs) to ensure data quality. This will be done both behaviorally, aimed at excluding subjects who do not meet our predefined criteria (see below), and physiologically, to test data quality (e.g., by assessing signal to noise ratio in the neural data, eye movement patterns in the eye tracking data, etc.). These data quality checks are orthogonal to the tested predictions by the theories. We will stop collecting data upon completing the predefined sample size. No further rejection of subjects will occur after this stage.

The exclusion criteria will include: (a) insufficient number of trials in each of the experimental conditions, due to excessive eye movements, muscular artifacts, movement, noisy recording, or subjects deciding to stop the experiments (<30 for M-EEG or <20 for fMRI. If analyses show that a good enough signal can be obtained with fewer trials, these numbers will be amended); and (b) low performance in the attention tasks. In Experiment 1, this translates into: <80% hits, >20% FAs for fMRI and M-EEG subjects; <70% hits, >30% FAs for iEEG patients. For Experiment 2 performance criteria, see below.

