The project is tripartite. At the time of submission of this study protocol, phase 1 is approximately halfway complete. In **phase 1**, all data will be acquired by theory neutral teams. To ensure replicability of the results, the entire dataset will be split into two halves, each with an equal mixture of data from each of the two labs for each recording technique (half of the participants tested in both labs). In **phase 2**, after evaluating data quality (see OSF preregistration), the first half of the data will be used for developing analysis tools (optimization of methods). The purpose of **phase 2** is to define the best analysis practices and to agree upon, in consultation with expert advisors, the detailed analysis protocols that will be preregistered in the final, unchangeable version of the preregistration. In our original protocol, phase 1 and phase 2 were planned to be conducted successively, yet due to delays in data acquisition caused by the COVID-19 pandemic of 2020–2021, now phase 1 and phase 2 will overlap. In **phase 3**, the replication phase, the second half of the data will be analyzed using these preregistered, agreed upon protocols, thereby allowing an in-house replication of the results obtained in phase 2. Data will be analyzed by the acquiring laboratories, a data analysis team composed of the two theory leaders, the center PIs (the three co-first authors leading this project), and a method-experts advisory panel. All data, meta-data, stimulation protocols, and analysis pipelines will be publicly released upon the publication of the final results via a combination of documents in OSF, raw data, processed data and analysis code, and protocol instructions and specifications in SLAB (data management and sharing plan are detailed below).

### Experiment 1

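### One figure of more than 90% power is given for all three modalities; under a conventional two-sided paired test it holds for fMRI and M-EEG with the labs combined, but not for iEEG

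*Protocol article*

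**What the plan says.** The Experiment 1 section on participants and sample size sets 50 subjects for fMRI, 50 for M-EEG and 25 for iEEG. It explains that "Samples sizes refer to total data that will be collected in each individual laboratory", and that "total sample sizes when the data is combined across labs will be one hundred for fMRI, one hundred for M-EEG, and fifty for iEEG". It then says "We estimate a 20% attrition related to data quality" and concludes that, even so, "since we will use a within-subject design", "this sample size will give us >90% power to detect differences of medium effect size", with Cohen's d of 0.5 or more. Modalities are not separated, and it is not said whether the figure refers to the per-lab or the combined sample. Alpha, sidedness and the standard deviation behind d are not given.

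On recruitment, the same section says: "We will stop collecting data upon completing the predefined sample size".

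The section on status and timeline adds that "the entire dataset will be split into two halves, each with an equal mixture of data from each of the two labs". The first half serves to develop the analyses; in phase 3, "the second half of the data will be analyzed using these preregistered, agreed upon protocols". No power is stated for a half.

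**The concern.** The iEEG sample is half the size of the other two, yet it carries the same power statement. A sample that is comfortably powered at 80 subjects need not be at 40, and clearly is not at 20. The numbers also halve again when the data are split, and the locked replication runs on one half.

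The study interprets negative results: absence of a predicted effect can count against a theory. A reader who takes the single figure at face value for iEEG would think that a real medium effect is missed less than one time in ten. With 20 patients, under the conventional assumptions, it would be missed in 43.5% of cases two-sided (100 − 56.5) or 30.5% one-sided (100 − 69.5).

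**Working it through.** **Inputs from the Protocol article.** Combined totals 100 / 100 / 50 (fMRI / M-EEG / iEEG); per lab 50 / 50 / 25; attrition 20%; d = 0.5 (the lower bound); within-subject comparison; two equal halves.

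**Assumptions, because the article does not state them.** Alpha 5%, shown two-sided and one-sided; d is the mean paired difference divided by the SD of the paired differences; lost subjects are not replaced.

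**Analysable subjects.**
- Combined: 100 × 0.8 = 80 for fMRI and for M-EEG; 50 × 0.8 = 40 for iEEG.
- Per lab: 50 × 0.8 = 40; 25 × 0.8 = 20.
- Per half, labs mixed: 80 / 2 = 40; 40 / 2 = 20.

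**Formula.** Power of a paired t-test with n − 1 degrees of freedom and noncentrality d√n. Two-sided: P(T > t₀.₉₇₅) + P(T < −t₀.₉₇₅). One-sided: P(T > t₀.₉₅).

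**Reproducing the stated figure.** For n = 80 the noncentrality is 0.5 × √80 = 4.47 and power is 99.3% two-sided, 99.7% one-sided. The claim of more than 90% holds for fMRI and M-EEG on the combined sample.

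**All samples, d = 0.5.**

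| Sample after attrition | n | d√n | Two-sided | One-sided |
|---|---|---|---|---|
| fMRI or M-EEG, combined | 80 | 4.47 | 99.3% | 99.7% |
| iEEG, combined | 40 | 3.16 | 86.9% | 92.8% |
| fMRI or M-EEG, per lab or per half | 40 | 3.16 | 86.9% | 92.8% |
| iEEG, per lab or per half | 20 | 2.24 | 56.5% | 69.5% |

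Ninety percent power at d = 0.5 needs 44 analysable subjects two-sided or 36 one-sided. The effect detectable with 90% power, two-sided, is d = 0.37 at n = 80, 0.53 at n = 40 and 0.76 at n = 20.

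**Sensitivity to attrition.** With every lost subject replaced, combined iEEG would have n = 50 and 93.4% two-sided. The stated figure, however, is expressly one that allows for attrition. One iEEG lab or half would then have n = 25: 67.0% two-sided, 78.3% one-sided.

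**Sensitivity to the definition of d.** If 0.5 is standardised by the within-condition SD, the effect on the paired scale is 0.5 / √(2(1 − r)), where r is the correlation between conditions. The article gives no r, so a range is shown (two-sided):

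| r | Paired-scale d | n = 40 | n = 20 |
|---|---|---|---|
| 0.3 | 0.42 | 74% | 43% |
| 0.5 | 0.50 | 87% | 56% |
| 0.6 | 0.56 | 93% | 66% |
| 0.7 | 0.65 | 98% | 78% |
| 0.8 | 0.79 | 99.8% | 92% |

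**The case against.** The strongest reply is that the shortfall depends on choices the article leaves open.

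- **Sidedness.** Many predictions are directional, such as higher late prefrontal activation for seen trials. With a one-sided 5% test every n = 40 case reaches 92.8%, so the single figure reproduces for all three modalities on the combined totals. A reader might infer that no modality reaches 90% in the second half; that does not follow, because fMRI and M-EEG do so one-sided.
- **Definition of d.** The article justifies its power by the within-subject design, which fits a d on the raw SD that gains from correlation between conditions. At r = 0.6, n = 40 gives 93% two-sided. So it cannot be said that iEEG misses 90% on every two-sided reading.
- **Halves.** The quoted sentence concerns the planned totals. A reader might infer that the plan promises a risk below 10% of missing a real effect in the iEEG replication; it makes no such promise. Nor is the first half used only for choosing a pipeline: the Discussion says that the hypotheses are also tested in it.
- **Reading of null results.** The statistical approach already uses Bayesian inference to handle absent effects and to weigh evidence across methods, and the caption of Fig 1 marks some negative outcomes as less conclusive. No rule lets one non-significant iEEG half decide between the theories.

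All four points stand and narrow the concern. They do not rescue the sentence as written: one unqualified figure covers samples of 80 and 40, or of 40 and 20 if read per lab, and the assumptions under which it would hold for iEEG are not given. At n = 20 with d on the paired differences, power is below 70% on either sidedness; among the correlations tried for the other definition, only r = 0.8 exceeds 90% two-sided.

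**Conclusion.** The point holds in a limited form. Under a two-sided 5% paired test with d on the paired differences, the stated power is right for fMRI and M-EEG with labs combined (99.3%) and is not delivered for iEEG. With labs combined the iEEG shortfall is about 3 points (86.9%) and disappears with a one-sided test (92.8%). On the per-lab reading it is large on either sidedness (56.5% or 69.5%), and on that reading fMRI and M-EEG also fall to 86.9% two-sided (92.8% one-sided).

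The second half has the per-lab numbers, so the power of the locked replication is well below the combined-sample figure, above all for iEEG. Since the article states no power for a half, this shows how far the figure reaches; it does not contradict it. All results rest on the assumed alpha, sidedness and standardiser, and would change with them as shown.

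**What to change.** Replace the sentence with one that states alpha, sidedness and the definition of d, and gives power by modality for the combined sample and for the replication half. If the two-sided paired test is what was meant, for example:

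*Two-sided 5% paired test, d = 0.5 on the paired differences, after 20% attrition. Combined sample: fMRI and M-EEG n = 80 each, 99%; iEEG n = 40, 87%. Replication half: fMRI and M-EEG n about 40 each, 87% (90% for d = 0.53); iEEG n about 20, 56% (90% for d = 0.76).*

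If a one-sided test or a raw-SD definition of d was intended, say so, give the assumed correlation where it applies, and use the matching figures. The change is wording only. It needs no more subjects; its cost is a less favourable stated power for iEEG.

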### Overview of operational hypotheses of the theories

Based on the opposing predictions of the theories, we will focus on testing three predictions. The first refers to **decodability of content of consciousness** (see analysis #1 below). Decoding will be tested for category as well as for orientation (which is a task irrelevant feature, because–as opposed to category–it is completely orthogonal to the task). As the stimuli are clearly visible in this experiment, the theories predict that information about the content of consciousness should be consistently found in the underlying neural substrates, even if the stimulus (or one of its features, like orientation) is task-irrelevant. Thus, according to GNW, such information should be found in nodes of prefrontal areas, while according to IIT it should be primarily found in posterior areas. The critical test of these predictions will accordingly be whether decoding of category and orientation generalizes from the task relevant (non-target) condition to the task irrelevant condition, within the predicted brain regions (PFC for GNW versus posterior hot zone for IIT). The second prediction refers to the **maintenance of a percept over time**, manipulated here via stimuli duration (see analysis #2 below). GNW predicts transient activity, reflecting an updating mechanism at stimulus onset and offset, while IIT predicts that the physical substrate of consciousness should remain in a similar activity pattern throughout the duration of the conscious experience (here, as long as the stimulus was presented). The third prediction focuses on **inter-areal communication** between different cortical regions during conscious perception (see analysis #3 below). GNW and IIT postulate different nodes (topologies) related to consciously perceiving a stimulus: for GNW, long-range synchrony is predicted between prefrontal and category-selective areas in high-level sensory cortex; for IIT synchronization is predicted within the posterior hot-zone, between category-selective regions in high-level sensory cortex and lower-level visual areas. Finally, an additional goal of this experiment is to **pinpoint the putative NCC**, while detecting areas that cannot be regarded as such, as their activity reflects task related processes (see analysis #4 below). This holds implications for the theories, as they differ in their predictions about the NCC (see‘*Neural Activations related to consciousness*’ above).

### Planned analyses and expected outcomes

#### 1. Multivariate decoding

To test which cortical areas contain information about clearly perceived stimuli across both task-relevant and task-irrelevant conditions, we will decode stimulus category (face/object or letter/false-font) and orientation (side view/front view) in the task-relevant non-target condition and then test for cross-task generalization of decoding to the task-irrelevant condition. Cross-task generalization from task-irrelevant to task-relevant condition will also be tested. Category decoding will always be carried-out within each stimulus class (faces vs. objects and letters vs. false-fonts), rather than between classes which would confound category and task (i.e., we will not decode faces vs. letters, or objects vs. false-fonts). Note that as opposed to information on category, which will sometimes be relevant and sometimes irrelevant, information on orientation will always be task-irrelevant during the entire experiment, despite being clearly seen. As mentioned above, here and in all analyses, we will use the first half of the data to optimize our analyses during phase 2 of the project (analysis development stage), including the selection of optimal decoding schemes (options include: linear SVMs, Bayesian SVMs, LDA, naïve Bayes, K-nearest neighbor, logistic regression, random forest).

GNW predicts that conscious content will be decodable from areas in the prefrontal cortex i.e., inferior frontal gyrus, middle frontal gyrus, and cingulate cortex [21, 51, 52], instantiating the global workspace, both for task relevant and task irrelevant conditions. Thus, GNW would expect transient information about category and orientation to be decodable from the PFC and global-workspace recipient regions in posterior and higher-order sensory cortex in task-relevant conditions, and for decoding to generalize between the task-relevant and task-irrelevant conditions and vice versa, specifically during the 300–500 ms time window. IIT predicts that content-specific NCCs will primarily be found in the posterior hot zone, independent of task-relevance, and makes no specific predictions as to the relevant time window. Thus, decoding of categories and orientations and cross-task generalization of decoding between the task-relevant and task-irrelevant conditions and vice versa should be maximal in posterior cortical areas.

#### 2. Activation patterns across stimulus durations

This analysis will target the relation between the temporal duration of the experience and the neural responses. Since subjects will observe clearly visible isolated stimuli at fixation and without competition, we assume that they will experience the stimuli for as long as they are on-screen, in particular because subjects’ fixation (via eye-tracking) will be constantly monitored (see the OSF page for a control experiment evaluating visibility of long-duration task irrelevant stimuli).

Here, we will evaluate the neural responses associated with the maintenance of a percept in consciousness. Specifically, we will investigate the temporal profile of activation evoked by stimuli of different durations as well as the temporal profile of informational content of the neural responses throughout the duration of the stimulus. For the former, we will compare activation levels between conditions (defined by stimulus duration) in four different time windows: (1) 300–500 ms, (2) 800–100 ms, (3) 1300–1500 ms, and (4) 1800–2000 ms using linear mixed models. For the latter, we will combine temporal generalization [53] and representational similarity analysis [RSA; 48] approaches: in long duration trials, stimulus category (as well as orientation) will be decoded in a temporal generalization fashion (testing for generalization of neural patterns containing the content specific information across time). Representational similarity analysis will then be employed to compare the resulting temporal generalization matrix to the predictions of the theories in the specified time windows.

GNW predicts ignitions within PFC following stimulus onset and possibly also during stimulus offset, constituting updates to conscious perception, with virtually no activity between updates [except for occasional stochastic bursts of spontaneous reactivation; 54]. Thus, for consciously perceived but task-irrelevant stimuli, neural activation is predicted to reflect an interaction between duration and time window in the PFC, such that activation is maximal in windows following stimulus onset and offset and minimal elsewhere. GNW further predicts that the patterns of activation will be consistent and content-specific between the windows where activation is expected to be maximum, whereas in the windows of minimal activation, there should be no content-specific activation. This translates in expected temporal generalization of decoding accuracy between the onset and offset burst with no generalization in between. This prediction can be translated in a model matrix to be correlated with the obtained temporal generalization results. IIT predicts sustained, content-specific activity patterns in posterior cortex throughout the duration of the percept (after the initial transient response). Therefore, activation levels within posterior areas should be higher for longer-duration (and consciously seen) than shorter-duration (and no longer seen) stimuli during analysis time windows 2 and 3. In addition, temporal generalization of decoding accuracy should be evident for as long as the stimuli are consciously experienced, and will be tested via correlation with a different model matrix than for GNW.

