#### 3. Temporal dynamics of the neural differences between stimuli reported as seen vs. unseen

We will track the neural dynamics of the difference between seen and unseen stimuli by running an ANOVA analysis with Visibility (seen/unseen) and Time (Early: 0–250 ms, Late: 250–500 ms). This analysis will not involve fMRI data due to the temporal precision required. We will test for a main effect of visibility and an interaction, with the latter testing a key prediction of GNW, i.e., a neural ignition for consciously perceived stimuli, reflected by a late (>250 ms) amplitude difference between dAT-seen and dAT-unseen trials. Prior to 250 ms, activation for dAT-unseen stimuli should be similar (if not equal) to dAT-seen activity, reflecting a fast feedforward sweep propagating from posterior to anterior cortices as well as local recurrent processing. The same is true for decoding of content. Therefore, late differences in amplitude in prefrontal areas between dAT-seen and dAT-unseen trials are expected, with little or no differences earlier in time. IIT does not make explicit predictions about the temporal dynamics differentiating seen from unseen conditions.

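### The PFC offset response is stated both as optional and as required, one analysis window is misprinted, and the Experiment 2 interaction does not by itself test similarity before 250 ms

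*Protocol article*

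**What the plan says.** **Experiment 1, offset response.** The article describes it in three ways.

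- In the introduction (Differential predictions of the theories, item 3), a brief ignition at stimulus offset is expected on the condition that the subject consciously detects the offset.
- In the Experiment 1 overview of operational hypotheses there is no condition: "GNW predicts transient activity, reflecting an updating mechanism at stimulus onset and offset".
- In planned analysis 2 (Activation patterns across stimulus durations) it becomes optional: "GNW predicts ignitions within PFC following stimulus onset and possibly also during stimulus offset". Between updates the section expects next to no activity, apart from occasional stochastic bursts.

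Planned analysis 2 then makes firm predictions for task-irrelevant stimuli. It says "neural activation is predicted to reflect an interaction between duration and time window in the PFC". The pattern described has its peaks after both the appearance and the disappearance of the stimulus, and its lowest values at all other times. For decoding, the section gives "expected temporal generalization of decoding accuracy between the onset and offset burst with no generalization in between", to be turned into a model matrix.

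**Experiment 1, windows.** The four analysis windows are printed as "1) 300–500 ms, (2) 800–100 ms, (3) 1300–1500 ms, and (4) 1800–2000 ms". The stimuli last 500, 1000 or 1500 ms. The activation prediction of Integrated Information Theory (IIT) uses windows 2 and 3.

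**Experiment 2, planned analysis 3.** The seen-unseen difference is to be followed by "running an ANOVA analysis with Visibility (seen/unseen) and Time (Early: 0–250 ms, Late: 250–500 ms"). The main effect of visibility and the interaction are tested, and the interaction is named as the test of a key GNW prediction, a late difference reflecting ignition. The text also expects seen and unseen activity to be alike, or nearly so, before 250 ms. It names no separate test of the early window.

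**The concern.** The adversarial design depends on each theory's predictions being fixed before the results are known.

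In Experiment 1, GNW's interaction and model matrix are derived from a response that the same section calls only possible. If PFC shows an onset response and nothing at offset, one side can cite the operational prediction as failed and the other can cite the hedge.

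The misprinted window matters to both theories. It is one of the two windows in IIT's activation comparison, and it is the offset window for the 500 ms stimuli.

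In Experiment 2, the prediction has two parts: similarity before 250 ms and a difference after it. An interaction compares the two differences and does not show that the early one is absent. A positive interaction could be reported as confirming the whole temporal prediction when the early part is false.

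**Working it through.** **1. Does the Experiment 1 interaction need the offset response?**

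Inputs: durations 500, 1000 and 1500 ms; windows as printed, with window 2 taken as 800–1000 ms. The onset response falls in window 1 (300–500 ms) for every duration. An offset response with the same 300–500 ms delay falls at duration + 300 to duration + 500 ms:

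- 500 ms stimulus: 800–1000 ms (window 2)
- 1000 ms stimulus: 1300–1500 ms (window 3)
- 1500 ms stimulus: 1800–2000 ms (window 4)

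Set the onset response to 1 and measure the interaction by its sum of squares (SS) over the 3 × 4 cell means:

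| Pattern in PFC | 500 ms | 1000 ms | 1500 ms | Interaction SS |
|---|---|---|---|---|
| Onset + full offset | 1 1 0 0 | 1 0 1 0 | 1 0 0 1 | 2.0 |
| Onset + half-size offset | 1 0.5 0 0 | 1 0 0.5 0 | 1 0 0 0.5 | 0.5 |
| Onset only | 1 0 0 0 | 1 0 0 0 | 1 0 0 0 | 0 |
| Onset + sustained, no offset | 1 0 0 0 | 1 1 0 0 | 1 1 1 0 | 0.83 |

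With onset only, all durations share one profile and the interaction is exactly zero. The last row shows that a sustained response, which GNW does not predict in PFC, also gives a nonzero interaction. The omnibus term therefore cannot identify the GNW pattern; the cell pattern has to be tested.

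**2. Window 2.**

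Lengths as printed (end minus start): 200, −700, 200 and 200 ms. Starts: 300, 800, 1300 and 1800 ms, so 500 ms apart. A 200 ms window starting at 800 ms ends at 1000 ms, and this is also the offset window of the 500 ms stimulus.

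**3. Visibility × Time in Experiment 2.**

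Let the seen-minus-unseen difference be zero up to time s (in ms, s ≤ 250) and D afterwards.

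- Early mean (0–250 ms) = D × (250 − s)/250
- Late mean (250–500 ms) = D
- Interaction = late − early = D × s/250

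| Start s | Early mean | Interaction |
|---|---|---|
| 100 ms | 0.6D | 0.4D |
| 150 ms | 0.4D | 0.6D |
| 200 ms | 0.2D | 0.8D |
| 250 ms (as predicted) | 0 | D |

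The step shape and the starts before 250 ms are assumptions, chosen to show the range.

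A simulation used paired differences in SD units (assumed two-sided 0.05, early-late correlation 0.5, 20,000 runs). Sample sizes follow from the article's numbers less 20% attrition: 100 × 0.8 = 80 (M-EEG combined), 50 × 0.8 = 40 (one M-EEG laboratory, or iEEG combined), 25 × 0.8 = 20 (one iEEG laboratory). The effect size 0.5 is the one in the article's power statement.

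| Early d, late d | Result | n = 80 | n = 40 | n = 20 |
|---|---|---|---|---|
| 0, 0.5 | significant positive interaction | 99% | 87% | 56% |
| 0.5, 1.0 | significant positive interaction | 99% | 87% | 56% |
| 0.5, 0.5 | significant interaction, either sign | about 5% | about 5% | about 5% |
| 0.5, 0 | significant negative interaction | 99% | 87% | 56% |

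The first two rows cannot be told apart by the interaction, although only the first agrees with the prediction before 250 ms. In the third row the main effect of visibility is significant in 100% (n = 80) and 94% (n = 40) of runs. An early difference equal to the late one thus removes the interaction, and a larger one reverses it.

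**The case against.** A reader might infer that these tests cannot count against GNW, or cannot arbitrate between the theories. The article does not support either reading. Whatever the status of the offset response, planned analysis 2 of Experiment 1 commits GNW to an onset ignition and to almost no activity or content between updates. Sustained PFC activity, or no onset ignition, would go against it. In Experiment 2 a null or reversed interaction would also go against it. That test was never meant to arbitrate: the article says the prediction is tested for GNW alone and has no direct bearing on IIT.

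The hedge may also have a reason, because the introduction makes the offset response conditional on conscious detection. A null interaction does contradict the firm sentence that follows the hedge. Fig 1, which sets out negative and less conclusive outcomes, is not shown, and analysis detail is left to the preregistration. Follow-up of a 2 × 2 interaction is often left to the full plan, and the window error is an evident dropped zero.

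Much of this stands and limits the point. The conflict over the offset response remains, because it lies in the predictions themselves, and the section on the analysis approach says these are explicit and fleshed out here. The planned Bayesian support for a missing effect helps only once the text says how that absence is scored. The early-similarity prediction is likewise in the article, while the effects named for testing do not address it directly.

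**Conclusion.** The point holds in a limited form, in three parts.

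- **Offset response.** It is conditional in one place, firm in another and optional in a third. The predicted interaction falls from an SS of 2.0 to 0 without it, so its absence has no settled meaning in the article. This assumes that the onset response falls in window 1 for all durations and that the offset response has the same delay.
- **Window 2.** The printed interval is impossible, and 800–1000 ms is the only value that fits. This is a correction, not a flaw in the design.
- **Experiment 2.** The interaction alone does not test similarity before 250 ms. It is blind to an early difference smaller than the late one, including a constant difference that starts before 250 ms (0.4D to 0.8D for starts at 100 to 200 ms). It is not blind to an early difference as large as the late one or larger.

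A fuller scoring rule may exist in Fig 1 or in the preregistration; neither was available.

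**What to change.** Make the changes in the preregistration amendment that is already planned before phase 3.

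1. Reconcile the three statements on the offset response (introduction, Experiment 1 overview, planned analysis 2), with sign-off by the GNW proponents. State whether the response is required, and how an absence supported by a Bayes factor is scored. The choice of commitment belongs to the proponents.
2. Test the predicted pattern of cells, and not only the omnibus duration-by-window interaction.
3. Correct window 2 to 800–1000 ms.
4. In Experiment 2, add a separate test of the early seen-unseen difference, with a Bayes factor or an equivalence bound, in a window fixed during phase 2. Call the full GNW temporal prediction supported only if the late difference is positive and the early test supports similarity.

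The cost is wording, the proponents' agreement and one extra test. The criterion for support also becomes stricter: a small sample may leave the early test inconclusive, and the full prediction would then not be called supported.
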